## Abstract

**Background:**

Young people account for more than a quarter of new HIV infections in the US, with the majority of cases among young men who have sex with men; young transgender women are also vulnerable to infection. Substance use, particularly alcohol misuse, is a driver of sexual transmission and a potential barrier to engagement in the HIV prevention and care continuum, however vulnerable youth are difficult to reach for substance use services due, in part, to complex social and structural factors and limited access to health care. The Community Prevention Services Task Force recommends electronic screening and brief intervention as an evidence-based intervention for the prevention of excessive alcohol consumption; however, no prior studies have extended this model to community-based populations of youth that are susceptible to HIV infection. This paper describes the study protocol for an electronic screening and brief intervention to reduce alcohol misuse among adolescents and young adults vulnerable to HIV infection in community-based settings.

**Methods:**

This study, Step Up, Test Up, is a randomized controlled trial of an electronic alcohol screening and brief intervention among youth, ages 16–25, who are vulnerable to HIV infection. Individuals who present for HIV testing at one of three community-based locations are recruited for study participation. Eligibility includes those aged 16–25 years, HIV-negative or unknown HIV status, male or trans female with a history of sex with men, and English-speaking. Participants who screen at moderate to high risk for alcohol misuse on the Alcohol Use Disorders Identification Test (AUDIT) are randomized (1:1) to either an electronic brief intervention to reduce alcohol misuse or a time-and attention-matched control. The primary outcome is change in the frequency/quantity of recent alcohol use at 1, 3, 6 and 12-month follow-up.

**Discussion:**

Testing of evidence-based interventions to reduce alcohol misuse among youth vulnerable to HIV infection are needed. This study will provide evidence to determine feasibility and efficacy of a brief electronically-delivered intervention to reduce alcohol misuse for this population.

**Trial registration:**

ClinicalTrials.gov number, NCT02703116, registered March 9, 2016.

## Background

Recent estimates of U.S. HIV incidence indicate that young people aged 13 to 24 account for nearly a quarter of new infections, with the majority of cases among young men who have sex with men (YMSM) [1, 2]. While official incidence statistics are not differentiated by transgender status, local estimates indicate extremely high rates of unrecognized HIV infection among young transgender women (YTW) as well [3–5]. Substance use, particularly alcohol misuse, has been identified as a driver of sexual transmission of HIV infection [6–9] and a potential barrier to engagement in HIV prevention and care among YMSM and YTW, however these youth are difficult to reach for substance use services due, in part, to complex social and structural factors and limited access to health care. YMSM and YTW, however, often seek HIV testing and other supportive services in community-based and outreach settings. These settings are underutilized as potential entry points for engagement in comprehensive care across the HIV prevention and care continuum, including pre-exposure prophylaxis (PrEP) for HIV-negative youth who are at risk of HIV acquisition.

Given the barriers to substance use screening and intervention among YMSM and YTW, interventions are needed that are client-centered and can be deployed in community settings. Motivational interviewing (MI) is a well-established client-centered behavioral change approach [10, 11]. The theoretical basis for MI draws in part on Rogerian concepts of psychotherapy that emphasize the need for self-exploration and patient-centeredness. The core of MI emphasizes that individuals must be empowered to change and that given the right set of circumstances they will gravitate toward more pro-social outcomes. The hallmarks of this method avoid telling individuals what to do, and instead create a space where the individual is allowed to explore their motivations through discrepancies that exist in their life (i.e. alcohol makes me feel relaxed, but I don’t like the way I treat others when I drink). By seeing these discrepancies, individual find a motivation to change and then move forward.

Expansion of MI-based or MI-informed approaches is taking place via initiatives to promote screening, brief intervention and referral to treatment (aka SBIRT). Electronic screening and brief intervention (eSBI) is a subset of SBIRT and essentially takes SBIRT into an electronic medium suitable for use in primary care and other generalist settings. The Community Prevention Services Task Force (CPSTF) recommends eSBI as an evidence-based intervention for the prevention of excessive alcohol consumption [12]. Most studies to date have tested this approach in health care (e.g., emergency room) and university settings with adults and young adults and for relatively short follow-up time (i.e., 6-months post intervention). In these settings, the CPSTF found sufficient evidence of efficacy across studies and age groups [12]. Little trial data exists for the use of eSBI in adolescents, minority racial/ethnic groups, or for longer periods of follow-up. To date no studies have tried to extend this model to populations such as YMSM and YTW, in community-based settings in which these youth tend to access services.

To capitalize on this opportunity, we propose to test a structural change to the HIV prevention and care continuum by integrating substance use screening and brief intervention into the traditional community-based HIV testing environment. We will couple standard HIV prevention with eSBI for at the point of HIV testing.

### Study objectives

The purpose of this study is to assess the feasibility, acceptability, and initial efficacy of eSBI in comparison to an electronic attention control intervention (i.e., promotion of good nutrition), coupled with standard HIV prevention, on alcohol use among YMSM and YTW in community-based HIV testing environments in Chicago. Secondary objectives are to assess intervention effects on sexual behavior, as well as engagement within the HIV prevention and care continuum, and to assess modification of the intervention effect by co-morbid mental health problems (i.e., symptoms of depression, anxiety, and exposure to trauma).

## Methods/design

### Design

This study is an individually randomized controlled trial (RCT) of eSBI among youth vulnerable to HIV infection. Using an electronic portal, all participants are screened for alcohol misuse and receive immediate feedback regarding their level of use (e.g., how their use compares to others, whether it exceeds “safe use” guidelines); those who screen for moderate to high alcohol use, including binge drinking, are then randomized to either electronic intervention or control modules. All participants, regardless of randomization status, are followed for 12 months with in-person visits conducted at 1, 3, 6 and 12-month intervals (Fig. 1).

**Fig. 1 Fig1:**
[figure not shown]
Step up, Test Up CONSORT Diagram

### Identification and recruitment of participants

Youth are recruited from HIV testing centers at the three primary sites in Chicago: the Division of Adolescent Medicine at Lurie Children’s Hospital, Howard Brown Health, and the Village at the University of Chicago. Individuals are eligible if they are: (a) aged 16 to 25 years, (b) interested in testing for HIV infection and (c) HIV-negative or HIV status unknown (per self-report; verified at the point of HIV testing), and (d) are MSM or a transgender woman who has sex with men (i.e., born male, identify as female/transgender, and at any point in the gender transition process); (e) English-speaking.

### Randomization

Upon enrollment, all participants complete HIV testing and screen for alcohol misuse using the Alcohol Use Disorders Identification Test (AUDIT) via an electronic portal, then receive immediate feedback regarding their level of use. Participants who screen moderate to high risk for alcohol misuse or endorse binge drinking on the AUDIT are randomized via computerized assignment in the portal (1:1) to either brief intervention modules to reduce alcohol misuse or a time-and attention-matched control (i.e., promotion of good nutrition). Study staff are blinded to random assignments.

### Description of the intervention: eSBI

Those randomized to the intervention complete modules on 11 topical areas (see Table 1), each with a single webpage, in an MI format. The intervention content was targeted to late adolescents and young adults in terms of voice and language (e.g., open, non-authoritarian, inclusive), contexts (e.g., school as well as work contexts) and reading level. Completion of the intervention is expected to take 10–15 min. The electronic intervention and control modules are delivered using a customized eSBI platform developed by Radiant Interactive Group (Laguna Niguel, CA). Radiant uses industry-standard data encryption and security to manage Protected Health Information recorded by their system.

**Table 1 Tab1:** eSBI Topical Areas

Webpage	Topic
1	Importance of change
2	Downsides of drinking
3	Confidence scale
4	Barriers to change
5	Explore ways to cut back or quit
6	Strategies for cutting back
7	Change motivators
8	1 year from now
9	Readiness to change
10	Summary slide
11	More information and/or referral

### Time- and attention-matched control: diet and nutrition

Those randomized to control complete a brief time-matched attention control intervention, also in MI format, of equal length, which encourages good nutrition.

### Standard-of-care prevention services

The standard HIV preventive care at each site includes youth-specific HIV testing and counseling and linkage navigation to PrEP or HIV care.

### Study assessments

Participants complete a baseline study visit comprised of standardized assessment via computer-assisted self-interviewing (CASI). Follow-up CASI assessments are conducted at 1, 3, 6, and 12-month follow-ups visits. Detailed contact information is collected in order to facilitate study retention.

Primary Outcome: Change in the frequency/quantity of self-reported recent alcohol use at 1, 3, 6 and 12-months on the Daily Drinking Questionnaire [13].

Secondary Outcomes: Sexual risk behavior is measured via a modified version of the AIDS-Risk Behavior Assessment [14] used in prior studies of YMSM and YTW [15, 16]. Engagement in HIV and/or PrEP care is measured via medical records abstraction of clinic visit continuity (i.e., at least two clinic visits over the 12-month observation period).

Moderators: Depression, anxiety, and trauma will be measured using the short version of the Center for Epidemiologic Studies Depression Scale (CES-D10), [17] 7-item Generalized Anxiety Disorder (GAD-7) [18] and Life Events Checklist (LEC), [19] respectively.

### Statistical analysis

Several data quality checks will be conducted prior to analysis, including analysis of descriptive statistics and graphic plots to detect appropriate range of variables and to detect missing data or invalid cases. All data are stored in a password-protected network server with daily back-up. In order to assess the initial efficacy of eSBI, the intervention and control groups will be compared on baseline characteristics to assess randomization, and variables for which there are significant group differences will be controlled in subsequent analyses. Extensions of generalized linear models (GLMs) will be used to assess the effect of the intervention on the primary alcohol-related outcomes at 1, 3, 6 and 12-month follow-up visits (post-intervention). Intervention effects will be examined in terms of average group differences over follow-up and using models with an indicator for intervention group, time, and a group by time interaction to determine whether the intervention and control groups differ in response to the intervention over time. Potential confounding and effect modification by sociodemographic characteristics and co-morbid conditions will be examined in exploratory analysis, and these variables will be selected for inclusion in multivariable models based on statistical significance and conceptual importance. All models will account for correlation among repeated measures on individuals over time as appropriate (e.g., by inclusion of subject-level random effects). Potential modifiers of the intervention effect on outcomes will be examined using models including two-and three-way interactions of intervention group, time, and moderator effects to determine whether intervention effects differ across levels of the modifying variables.

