### Sample size calculation

We propose to enroll 450 participants and have estimated 80% power to detect effects for our primary (alcohol use) and secondary (PrEP uptake) outcomes using formulas for longitudinal study designs with attrition [20]. Calculations assume an exchangeable covariance structure, measurements at baseline and 4 follow up points, and within-subject correlation among repeated measurements (rho) of 0.5. All estimates use two-sided tests of significance and alpha of 0.05. With a retention rate of 85% at 1 year, we would have > 80% power to detect effect sizes (Cohen’s d) of 0.23 (small effect size) [21] or greater for between-group comparison of continuous measures of alcohol consumption and other substance use. For binary outcomes (i.e. any binge drinking), we would have ≥80% power to detect differences in proportions of 10% or greater when the proportion in the control group ranges from 25 to 30%, using a repeated measures framework with 4 follow-up measures and assumptions stated above. Thus, this study is powered to detect small to medium effect sizes that are consistent with or smaller than others reported in the literature [22].

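### Covariates for the efficacy analysis are picked by significance tests of baseline balance, which makes the primary model data-dependent and leaves available precision unused; fix baseline drinking as a covariate instead

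*Protocol article*

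**What the plan says.** In the Statistical analysis section of the protocol article, a sentence about assessing initial efficacy has the arms compared on baseline characteristics as a check on the randomisation, and adds that "variables for which there are significant group differences will be controlled in subsequent analyses". No significance level is given for these comparisons.

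The efficacy analysis uses extensions of generalised linear models. It looks at the mean between-arm difference across follow-up and at "models with an indicator for intervention group, time, and a group by time interaction". Baseline drinking is not named as a covariate, and it is not excluded.

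The same section describes a second route for covariates. Sociodemographic characteristics and co-morbid conditions are examined in an exploratory analysis, and "these variables will be selected for inclusion in multivariable models based on statistical significance and conceptual importance".

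Under Study assessments the primary outcome is "Change in the frequency/quantity of self-reported recent alcohol use at 1, 3, 6 and 12-months on the Daily Drinking Questionnaire". The Sample size calculation lists a baseline measurement alongside the four follow-ups.

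**The concern.** Assignment is by computer, 1:1, so any baseline difference between arms is a chance difference. A significance test of it tells the analyst nothing about which variables matter. A covariate earns its place in a randomised comparison by predicting the outcome, and this rule does not ask about that. A strong predictor that happens to be balanced is left out; a weak one that happens to differ is put in.

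Two things are at stake. The composition of the primary efficacy model depends on the observed data. And baseline drinking, which under the plan's own correlation assumption is a useful predictor of later drinking, may be left unused as a covariate in a trial that seeks a small effect with power only just above 80%.

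**Working it through.** **Inputs** (Sample size calculation unless noted)
- "We propose to enroll 450 participants"; 1:1 allocation (Randomization). I take this as 225 randomised per arm. That is an assumption, because only those who screen positive for alcohol misuse are randomised.
- 85% retained at one year: 225 × 0.85 = 191.25 per arm.
- m = 4 follow-ups, exchangeable correlation rho = 0.5.
- "All estimates use two-sided tests of significance and alpha of 0.05". This refers to the power estimates; I assume the same level for the baseline tests.
- Target: "we would have > 80% power to detect effect sizes (Cohen’s d) of 0.23".

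**Step 1. Reproduce the plan's figure, without baseline adjustment.**
Variance factor of the mean of m exchangeable measures: (1 + (m − 1)rho)/m = (1 + 3 × 0.5)/4 = 0.625.
Per arm: 2 × 0.625 × ((1.960 + 0.842)/0.23)² = 185.5, so 186. Total 372; 372/0.85 gives 438, within 3% of 450.
With 191.25 per arm: SE = √(2 × 0.625/191.25) = 0.0808. Detectable d = 2.802 × 0.0808 = 0.2265. Power at d = 0.23 is Φ(0.23/0.0808 − 1.960) = 81.2%.
The stated d of 0.23 therefore reproduces with no baseline covariate.

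**Step 2. Baseline drinking always in the model.**
Variance factor: 0.625 − rho² = 0.625 − 0.25 = 0.375, a 40% reduction.
SE = √(2 × 0.375/191.25) = 0.0626. Detectable d = 2.802 × 0.0626 = 0.175. Power at d = 0.23 is 95.7%.

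**Step 3. A plain change score.**
Variance factor: 0.625 + 1 − 2 × 0.5 = 0.625. At rho = 0.5 this equals no adjustment (81.2%).

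**Step 4. The rule as written, simulated.** 20,000 trials per setting, 191 per arm, normal complete data, baseline drinking as the only candidate, entered only if its two-sided p < 0.05.
At rho = 0.5:
- baseline enters in 4.7% to 5.1% of trials;
- power at d = 0.23 is 82.5%, against 95.6% with baseline always in;
- type I error is 3.8% and 95% interval coverage about 96%;
- the true SE is 0.076 against a mean reported SE of 0.080, so intervals are slightly too wide.

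**Step 5. Sensitivity to rho** (0.3 and 0.7 are my assumptions). Simulated power at d = 0.23:

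| rho | Follow-up mean, unadjusted | Change score | Rule on follow-up mean | Rule on change score | Baseline always in | Type I error, rule on follow-up mean |
|---|---|---|---|---|---|---|
| 0.3 | 90.0% | 66.6% | 90.8% | 69.1% | 95.0% | 4.5% |
| 0.5 | 80.8% | 80.9% | 82.5% | 82.6% | 95.6% | 3.8% |
| 0.7 | 72.1% | 95.6% | 74.5% | 96.2% | 98.8% | 3.2% |

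Fixed adjustment has the highest power in every row, whichever way the change outcome is read.

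**The case against.** The strongest reply is that baseline drinking may already be in the analysis by another route. The primary outcome is defined as change, which could mean subtraction of baseline, and the sample size section counts baseline among the repeated measurements. The analysis section speaks of post-intervention visits, which points the other way. The text is ambiguous, so the 5% entry rate is conditional: it needs the balance test to be the only route for baseline drinking as a covariate, and a 0.05 level that the article does not state. That part of the objection stands. It does not remove the gain, because at the plan's own rho a change score performs no better than no adjustment. Baseline as a repeated outcome with the arm means left free does not recover the full gain either.

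Four stronger readings are tempting, and the documents do not support them.
- *The error rates are unsafe.* The distortion is conservative and small, and no bias in the effect estimate is shown.
- *The trial is underpowered because of the rule.* At the plan's own inputs the stated power of over 80% is met.
- *A large loss at rho = 0.7 (74% against 99%).* This holds only if the outcome is the raw follow-up level. With a change score the contrast is 95.7% against 98.8% by formula, and 0.7 is not the plan's value.
- *The second selection rule also drives the primary model purely on p-values.* The article introduces it as exploratory, limits it to sociodemographic and co-morbid variables, and adds conceptual importance as a criterion.

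A full analysis plan, not shown, may fix the covariates. That would supply a missing detail, but the article states a rule and that rule would still have to be withdrawn.

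**Conclusion.** The point holds as a should-fix. The article states a rule that picks covariates for the efficacy analysis by chance imbalance. The cost is a data-dependent primary model and unused precision: at rho = 0.5, 40% of the variance of the time-averaged difference, or a type II error of about 18% where about 4% is available from data already collected.

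The size rests on 225 randomised per arm, 85% with all four follow-ups, exchangeable correlation 0.5, a 0.05 level for the balance tests, and the rule being the only route for baseline drinking as a covariate. That baseline drinking is a strong predictor is inferred from the assumed rho; the article does not say so. The simulation used normal, complete outcomes and one candidate covariate. Drinking measures are likely to be skewed, so the gain in practice could differ from these figures.

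**What to change.** 1. Delete the significance tests of baseline differences and the adjustment they trigger. Report baseline characteristics by arm descriptively.
2. Prespecify the baseline value of the outcome (baseline Daily Drinking Questionnaire consumption for the primary outcome) as a covariate in every primary efficacy model, whatever imbalance is observed.
3. State how baseline enters given that the outcome is defined as change, so that one model follows from the text.
4. Keep any model whose covariates are selected on significance explicitly exploratory, as the section already partly indicates.

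Adjusting for recruitment site or AUDIT score is optional; if wanted, it should be fixed in advance too.

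The cost is about one paragraph of analysis wording. Baseline drinking is already measured, so no new data and no additional participants are needed.

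### Intervention effects are examined by both an average group difference and a group-by-time interaction, with neither ranked and the place of baseline in time left open

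*Protocol article*

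**What the plan says.** The Statistical analysis section first defines the modelled data as the "primary alcohol-related outcomes at 1, 3, 6 and 12-month follow-up visits (post-intervention" assessments. It then gives two routes to the treatment effect in one sentence. The first is "Intervention effects will be examined in terms of average group differences over follow-up". The second is a model with terms for group and time and "a group by time interaction to determine whether the intervention and control groups differ in response to the intervention over time". Neither route is called primary, and the section does not say whether the baseline measurement is one of the time points.

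The same section adjusts for baseline variables only where the arms turn out to differ significantly. The baseline value of the outcome is therefore not a fixed covariate.

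The Sample size calculation section gives power above 80% for "effect sizes (Cohen’s d) of 0.23 (small effect size) [21] or greater for between-group comparison". It assumes an exchangeable covariance, rho = 0.5, and a baseline plus four follow-up measurements. On the error rate it says "All estimates use two-sided tests of significance and alpha of 0.05", with no division between analyses. The Study assessments section describes the primary outcome as a change in drinking on the DDQ.

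**The concern.** The two analyses answer different questions. The average difference asks whether the arms differ after the intervention. An interaction fitted to the follow-up visits alone asks whether that difference changes from month 1 to month 12. The intervention is a single session of 10 to 15 minutes that precedes every follow-up visit, so a benefit present at month 1 and fully maintained gives an interaction of zero. A benefit that wears off can give a strongly significant one.

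With no ranking, two things could go wrong at reporting. A durable benefit could be summarised by a null interaction, or efficacy could be claimed on whichever analysis is significant. The stated power and alpha belong to one test, and the article does not say that this test decides.

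**Working it through.** **Inputs.** From Sample size calculation: "We propose to enroll 450 participants"; "With a retention rate of 85% at 1 year"; rho = 0.5, exchangeable; two-sided alpha 0.05; d = 0.23. From Randomization: 1:1 allocation. My assumptions: all 450 are randomised; the 85% retained supply complete data, so n = 450 × 0.85 / 2 = 191.25 per arm; the outcome is continuous with SD 1; the effect is a constant 0.23 at all four follow-ups unless stated; tests use a normal or chi-square approximation.

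**1. Reproducing the stated power.**
- Variance of a participant's mean over four visits: (1 + 3 × 0.5) / 4 = 0.625.
- SE of the group difference: sqrt(2 × 0.625 / 191.25) = 0.0808.
- z = 0.23 / 0.0808 = 2.845, so power = Phi(2.845 − 1.960) = 0.81. The smallest effect detectable with 80% power is 0.226, which rounds to the stated 0.23.
- A single visit would give only 0.61, so the stated figure is not for one time point. The mean follow-up minus baseline has variance 0.625 + 1 − 2 × 0.5 = 0.625, which is the same. At rho = 0.5 the stated power therefore fits either the average difference or a post-minus-baseline contrast.

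**2. Interaction on follow-up visits only.** A constant effect has zero contrast between visits. The noncentrality is 0 and the rejection rate is 0.05, for a linear or a 3-df test.

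**3. Interaction with baseline as a level of time** (effects 0, 0.23, 0.23, 0.23, 0.23).
- Linear in months 0, 1, 3, 6, 12: mean 4.4, sum of squared deviations 93.2. Contrast = 0.23 × 4.4 = 1.012. Its SE = sqrt(2 × 0.5 × 93.2 / 191.25) = 0.698. z = 1.45, power 0.31.
- Linear in visit number: noncentrality 4.05, power 0.52.
- Categorical, 4 df: noncentrality 0.23² × 191.25 / (2 × 0.625) = 8.09, power 0.61.
- Post-minus-baseline, 1 df: noncentrality 8.09, power 0.81.

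| Test, sustained d = 0.23 | 191.25 per arm | 225 per arm |
|---|---|---|
| Average over follow-up | 0.81 | 0.87 |
| Interaction, follow-up visits only | 0.05 | 0.05 |
| With baseline, linear in months | 0.31 | 0.35 |
| With baseline, linear in visit number | 0.52 | 0.59 |
| With baseline, categorical 4 df | 0.61 | 0.69 |
| With baseline, post-minus-baseline | 0.81 | 0.87 |

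**4. A fading effect, for illustration.** Let the effect be 0.46 × (1 − month/12), so that it is zero at month 12 and averages 0.249 over the four visits. With 191.25 per arm, the follow-up-only linear interaction has power 0.99 and the average difference 0.87. A significant interaction can therefore mean that the benefit has been lost.

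**5. Error rate if either test at 0.05 counted.** On follow-up visits only, the average and the linear slope are uncorrelated under exchangeability: 1 − 0.95² = 0.0975. With baseline in the model the rate is 0.096 to 0.0975, depending on how time is coded.

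**6. Always adjusting for baseline.** The variance becomes 0.625 − 0.5² = 0.375. SE = sqrt(2 × 0.375 / 191.25) = 0.0626, z = 3.67, power = Phi(3.67 − 1.96) = 0.96.

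**The case against.** In the plan's favour, the section states no success rule. Effects are to be examined, the average difference comes first, and the interaction is given its proper purpose of showing whether response differs over time. A null interaction beside a significant average difference correctly reports a sustained effect, and the 5% rejection rate is then simply the size of a test whose null hypothesis is true. The primary outcome is a change and the sample size section counts baseline as a measurement. If time includes baseline, the interaction does carry the treatment effect, and a post-minus-baseline contrast loses no power. Coding of time and ranking of tests often sit in a fuller plan, which is not shown.

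Most of this stands. A reader might infer that the interaction is no test of efficacy at all, or that the plan doubles its false-positive rate. The article supports neither. The first holds only if time excludes baseline. The second needs a rule that either test suffices, and the article contains none. Nor can the article be said to have powered only the average difference, since at rho = 0.5 its figure fits the post-minus-baseline contrast equally well.

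What remains is that the article itself places two analyses under the heading of intervention effects without ranking them. The meaning of the second, and its power for a sustained effect anywhere from 0.05 to 0.81, depends on a choice the text leaves open. The rule of adjusting only for significant imbalance is also stated outright, so it is not a detail left to another document.

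**Conclusion.** The point holds as a worthwhile clarification, not as an error that invalidates the plan. The average difference over follow-up delivers the stated power (0.81 at d = 0.23). An interaction on the post-intervention visits cannot detect a sustained effect. With baseline as a level of time, its power runs from 0.31 to 0.81 according to coding. A type I error of about 9.7% is the consequence only if significance on either test were accepted as efficacy.

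These figures rest on the article's exchangeable covariance with rho = 0.5, on 191.25 analysed per arm, on a constant effect and on a continuous outcome with SD 1. The adjusted power of 0.96 also needs the correlation of 0.5 to hold between baseline and every follow-up visit, including month 12.

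**What to change.** Name the group difference averaged over months 1, 3, 6 and 12 as the single primary efficacy test at two-sided 0.05. Adjust it for the baseline DDQ score whether or not the arms differ at baseline. Make the group-by-time interaction secondary: treat time as categorical, say whether baseline is one of its levels, and report visit-specific differences with confidence intervals to show whether the effect fades.

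The cost is wording only. No extra data or participants are needed, and power rises from about 0.81 to about 0.96 under the stated correlation. Keeping both tests at 0.025 each would instead lower the unadjusted average test to about 0.73. The small downside is that a purely short-lived effect is diluted in the average, though it would still show in the visit-specific estimates.
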